### **10.3. Timing for Analysis**

We will carry out an interim analysis once the immunogenicity data at D28 post boost becomes available, and a final analysis will be done at the end of the study when immunogenicity at all time points are available.

### **10.4. The Level of Statistical Significance**

There will be no statistical significance testing for primary endpoints of safety. For secondary endpoints of immunogenicity, the level of significant will be two-sided 0.05.

### **10.5. Procedure for Accounting for Missing, Unused, and Spurious Data.**

All available data will be included in the analysis.

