#### 6.3.3. Re-vaccination exclusion criteria

Participants who develop COVID-19 symptoms and have a positive PCR test after the first vaccination can only receive a booster dose after a minimum 4 weeks interval from their first PCR positive test, provided their symptoms have significantly improved. The decision to proceed with booster vaccinations in those cases will be at clinical discretion of the investigators. For participants who are asymptomatic and have a positive PCR test, a minimum of 2 weeks from first PCR positivity will be required before boosting.

The following AEs associated with any vaccine, or identified on or before the day of vaccination, constitute absolute contraindications to further administration of an IMP to the participant in question. If any of these events occur during the study, the participant will be withdrawn from the study and followed up by the clinical team or their GP until resolution or stabilisation of the event:

- Anaphylactic reaction following administration of vaccine
- Pregnancy

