#### 7.4.7. Randomisation, blinding and code-breaking

Participants will be randomised on a 4:1:4:1 basis to receive ChAdOx1 nCoV-19 5.0x10^10vp/ 5.0x10^10vp (boost at D28) or MenB/MenB (boost at D28) or ChAdOx1 nCoV-19 5.0x10^10vp/ 5.0x10^10vp (boost at D84) or MenB/MenB (boost at D84). A block randomisation with block size of 10 will be applied. The randomisation will be stratified by recruitment site and age group.

The trial staff administering the vaccine will not be blinded. Vaccines will be prepared out of sight of the participant and syringes will be covered with an opaque object/material for administration to ensure blinding.

If the clinical condition of a participant necessitates breaking the code, this will be undertaken according to a trial specific working instruction and group allocation sent to the attending physician, if unblinding is thought to be relevant and likely to change clinical management. If a participant becomes eligible for routine immunisation then they will need to be unblinded, and if they were in the control group they will be advised to receive a COVID-19 vaccine as per NHS guidelines. They will also be offered the opportunity to complete their course of MenB vaccination if they have not already received their second dose. If participants were in the ChAdOx1 arm, they will be offered the opportunity, in the trial, to complete their course of ChAdOx1 vaccination, if they have not already received their second dose. All unblinded participants will be allowed to stay on in the trial for follow up visits, both for safety and immunogenicity data.

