### **10.2. Analysis population**

All participants received at least one dose of study vaccines will be included in the analysis of safety and will be analysed according to vaccine received.

The immunogenicity analyses will include participants who are seronegative to the spike protein at baseline and received both prime and boost vaccine. Sensitivity analyses of immunogenicity data will be conducted including all vaccinated participants regardless of seropositivity status and protocol deviations.

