| 8             | 7.0                  | 10 th May 2021       | [name], [name]                        | Change to booster interval from 84 days to 112 days for participants who are yet to receive booster vaccines.                                                                                                                                                                                                                                                                                                                                                                  |
| 9             | 8.0                  | 28 th May 2021       | [name], [name]                        | Addition of a group holding rule for Thrombosis.

Clarification that participants unblinded due to being offered vaccine in national roll out who received a single dose of ChAdOx1 nCov-19 can receive the second dose in the trial.

Staggered booster dosing over a two week period per age group.                                                                                                                                                              |
| 10            | 8.1                  | 16th July 2021                  | [name]                                        | Addition of text allowing participants to withdraw from study procedures (e.g. blood taking) but remain a participant in the trial particularly to facilitate collection of safety data. These visits may be conducted by telephone.                                                                                                                                                                                                                                           |
| 11            | 8.2                  | 14 th September 2021 | [name]                                        | Re-inserting deleted values in Table 11, inserting reference ranges for CRP. Following a government announcement on 13 th September 2021 that teenagers aged 12-15 years of age will be offered one dose                                                                                                                                                                                                                                                            |

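### Sections 10.2 and 10.5 set no rule for immunogenicity samples taken after a non-trial COVID-19 vaccine or a SARS-CoV-2 infection, so these samples count as response to the allocated vaccine

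*Protocol*

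**What the plan says.** Section 10.2 (Analysis population): "The immunogenicity analyses will include participants who are seronegative to the spike protein at baseline and received both prime and boost vaccine". It sets no explicit criterion for infection or COVID-19 vaccination after baseline. The only sensitivity analysis widens the set: "Sensitivity analyses of immunogenicity data will be conducted including all vaccinated participants regardless of seropositivity status and protocol deviations".

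Section 10.5, on missing, unused and spurious data, consists of one sentence: "All available data will be included in the analysis".

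Other sections foresee spike exposure from outside the trial:

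- Section 7.4.7: a participant who becomes eligible for routine immunisation is unblinded, and "if they were in the control group they will be advised to receive a COVID-19 vaccine as per NHS guidelines". Controls may still complete MenB. Then: "All unblinded participants will be allowed to stay on in the trial for follow up visits, both for safety and immunogenicity data".
- Section 8.9: unblinding so that a participant can join a national programme is not restricted to controls.
- Appendix A, amendment 11, records the government announcement of 13 September 2021 that "teenagers aged 12-15 years of age will be offered one dose" of another COVID-19 vaccine.
- Section 6.3.3: a participant with symptomatic, PCR-confirmed infection after the prime "can only receive a booster dose after a minimum 4 weeks interval from their first PCR positive test". Such a participant can therefore still receive both doses and stay in the main set.
- Section 5: the trial does no PCR testing, so infections are known only from community tests that participants report.

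**The concern.** The secondary endpoints measure anti-spike antibody, neutralisation and spike-specific T cells. A non-trial spike vaccine or an infection raises the same quantities. Section 6.3.2 already accepts this before enrolment: it excludes earlier COVID-19 and earlier coronavirus vaccines, the latter because they may affect interpretation. The same exposures after D0 have no rule.

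Two distinct consequences follow.

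1. **Attribution.** A MenB control who takes a national-programme vaccine and completes MenB remains in the main set, and the resulting titre is read as a MenB response. In ChAdOx1 recipients, late GMCs mix persistence of the trial vaccine with later exposures.
2. **Group 1 v Group 2.** The 28-days-post-boost sample comes much later after the prime in Group 2, so more infections can precede it. Section 10.1.2 fixes the post-boost GMC and seroconversion on that sample, and section 10.4 sets a two-sided 0.05 level for immunogenicity.

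**Working it through.** **The plan's own figure.** The one design probability stated is for adverse events: n = 60 and rate 5% give 1 − 0.95^60 = 95.4%, which agrees with the stated more than 90%. No figure is stated for immunogenicity.

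**Days from prime to the 28-days-post-boost sample (Tables 5a and 5b).**

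- Group 1: boost at D28-42, sample 21-35 days later, so 28 + 21 = 49 to 42 + 35 = 77 days (nominal 56).
- Group 2: boost at D112-140, sample 21-35 days later, so 112 + 21 = 133 to 140 + 35 = 175 days (nominal 140).

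The windows do not overlap, and the nominal ratio is 140/56 = 2.5.

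**Days from prime to the D364 sample.** Group 1: 28 + 306 = 334 to 42 + 366 = 408. Group 2: 334 to 394. Exposure is about equal, so the imbalance does not carry over.

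**Does the September 2021 roll-out reach the post-boost sample?** The protocol gives no priming dates. I assume 9 February to 8 April 2021, inferred from the amendment log and the recruitment halt. Nominal D140 is then 29 June to 26 August 2021, before 13 September. Only samples near the end of the window (D175, 3 August to 30 September) could follow it. The roll-out therefore affects mainly later samples, and the imbalance between Groups 1 and 2 comes mainly from infection.

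**Size at the post-boost sample (assumed inputs).** Let m be the infection risk per 28 days and k the fold rise in an affected sample. The affected share is f = 1 − (1 − m)^(days/28). The log GMC shifts by f·ln k, so the spurious Group 2/Group 1 ratio is k^(f2 − f1). The false-positive rate is for Mann-Whitney with no true difference, 4,000 simulated trials, 60 v 60, SD of ln titre 0.9. That SD is based on the adult data in Table 1b: for the longest interval, ln(72,343.4/55,180.1)/(2 × 1.96) × √154 = 0.86, and the four rows span 0.72-1.06.

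| m per 28 days | f, Group 1 | f, Group 2 | GMC ratio, k = 5 to 10 | False-positive rate, k = 5 to 10 |
|---|---|---|---|---|
| 0.5% | 1.0% | 2.5% | 1.02 to 1.04 | not simulated |
| 1% | 2.0% | 4.9% | 1.05 to 1.07 | 5.4% to 5.8% |
| 2% | 4.0% | 9.6% | 1.10 to 1.14 | 7.3% to 8.3% |
| 4% | 7.8% | 18.5% | 1.19 to 1.28 | 12.8% to 15.6% |

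The simulation error at 5% is √(0.05 × 0.95/4,000) = 0.34 percentage points, so the 1% row is close to nominal.

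**Size at D364 (assumed inputs).** If 10% to 50% of samples follow another exposure and k is 3 to 10, the GMC is inflated by 3^0.1 = 1.12 to 10^0.5 = 3.16.

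**MenB controls.** Here k may be far larger, because controls start seronegative. As an illustration from Table 1b, adults in the shortest-interval row rose from 60.51 to 8,734.08 after one ChAdOx1 dose, 144-fold. If one of 15 controls in a group had a rise of that order, the control GMC would be multiplied by 144^(1/15) = 1.39. This borrows an adult figure for a different product and shows scale only.

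**The case against.** **This belongs in the SAP.** The protocol announces a detailed SAP and describes its own methods as brief. That is fair for operational detail. But the protocol itself fixes the analysis set, the all-data rule and the retention of unblinded participants, and a later censoring rule would have to be squared with that text.

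**Section 10.5 is over-read.** It cannot override section 10.2, which already leaves out baseline-seropositive and single-dose participants. The natural reading is all available data within each set. I accept that, but the set still has no criterion that removes the affected samples.

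**The main set already drops protocol deviations.** The wording of the sensitivity analysis implies that some are dropped, without saying which. Vaccination permitted by section 7.4.7 and infection are not clearly deviations.

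**The effects are small or conservative.** Contaminated controls shrink the ChAdOx1-MenB contrast. In the adult data the longest interval exceeds the shortest by 63,181.59/22,222.73 = 2.8-fold, well above the 1.02 to 1.28 range. Both points stand and limit the severity.

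**Censoring has a cost.** It conditions on post-randomisation events that the vaccine may itself influence, and an all-data analysis is a recognised strategy. This is a reason to report both.

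A reader might also infer that non-trial vaccination biases the longer-interval arms generally. The documents do not support that. The dated roll-out falls after nominal D140 on the inferred dates, D364 exposure is about equal, the announcement covers ages 12-15, and Groups 3 and 4 have no same-age D28-boost comparator.

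**Conclusion.** The point holds in this limited form. Following sections 10.2 and 10.5 as written, samples taken after a non-trial COVID-19 vaccine or an infection are credited to the allocated vaccine, and no planned analysis removes them. That conclusion rests on the text and needs no assumed rate.

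The imbalance between Groups 1 and 2 at the post-boost sample is structural (49-77 v 133-175 days after prime), but its size is unknown. The ratios and false-positive rates above depend on assumed m and k, and at 1% risk per 28 days the test stays near its nominal level.

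This should be fixed, but it is not critical: immunogenicity is secondary, and the primary safety objective has no formal hypothesis. A reader might infer that SAE attribution is equally compromised. That is weak, because safety is descriptive (section 10.1.1) and section 9.9 already requires concomitant therapy and other causes to be considered for each event.

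**What to change.** Amend sections 10.2 and 10.5, and align the SAP, so that the main immunogenicity analysis censors each participant's samples from the earliest of:

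- the first non-trial COVID-19 vaccine dose;
- the first reported positive SARS-CoV-2 test;
- the first sample showing anti-nucleocapsid seroconversion, where that assay is available.

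Report the analysis without censoring as the sensitivity analysis, and tabulate the number of censored samples by group and visit. The anti-nucleocapsid condition is needed because section 4 lists that assay as exploratory. It is useful because infections are otherwise only self-reported, and the trial vaccine carries the spike antigen only. Splitting SAE and AESI tables at the first non-trial dose is optional.

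The cost is wording and programming. No visit, blood draw or boosting rule changes. Fewer samples remain in the main analysis: at the post-boost visit, with m from 0.5% to 4% per 28 days, 60f gives 0.6 to 4.7 of 60 lost in Group 1 and 1.5 to 11.1 of 60 in Group 2, and 90f gives 2.2 to 16.6 of 90 in Groups 3 and 4 combined. Losses at D364 in 12-17 year olds may be larger. Infections that are neither reported nor detected by the assay stay in. The exclusion is post-randomisation and may be selective, which is why the all-data result should be shown beside it.

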## **11. DATA MANAGEMENT**

Direct access will be granted to authorised representatives from the Sponsor, host institution and the regulatory authorities to permit trial-related monitoring, audits and inspections. Safety data will be made available to AstraZeneca to facilitate pharmacovigilance monitoring of this vaccine. The study protocol, documentation, data and all other information generated will be held in strict confidence. No information concerning the study or the data will be released to any unauthorised third party, without prior written approval of the sponsor.

### **11.1. Data Handling**

The Chief Investigator will be responsible for all data that accrues from the study.

All study data including participant diary will be recorded directly into an Electronic Data Capture (EDC) system (e.g. OpenClinica, REDCap, or similar) or onto a paper source document for later entry into EDC if direct entry is not available. This includes safety data, laboratory data and outcome data. Any additional information that needs recording but is not relevant for the CRF (such as signed consent forms etc.) will be recorded on a separate paper source document. All documents will be stored safely and securely in confidential conditions.

All adverse event data (both solicited and unsolicited) reported by the participant will be entered onto a participant's electronic diary card (eDiary) for a maximum of 28 days following administration of the IMP. The eDiary provides a full audit trail of edits and will be reviewed at each review time-points indicated in the schedule of events. Any adverse event continuing beyond the period of the diary will be copied into the eCRF and followed to resolution, if there is a causal relationship to the IMP, or to the end of the study if there is no causal relationship.

The participants will be identified by a unique trial specific number and code in any database. The name and any other identifying detail will NOT be included in any trial data electronic file.

The EDC system (CRF data) uses a relational database (MySQL/ PostgreSQL) via a secure web interface with data checks applied during data entry to ensure data quality. The database includes a complete suite of features which are compliant with GCP, EU and UK regulations and Sponsor security policies, including a full audit trail, user-based privileges, and integration with the institutional LDAP server. The MySQL and PostgreSQL database and the webserver will both be housed on secure servers maintained by the University of Oxford IT personal. The servers are in a physically secure location in Europe. Backups will be stored in accordance with the IT department schedule of daily, weekly, and monthly retained for one month, three months, and six months, respectively. The IT servers provide a stable, secure, well-maintained, and high capacity data storage environment. REDCap and OpenClinica are widely-used, powerful, reliable, well-supported systems. Access to the study's database will be restricted to the members of the study team by username and password.

### **11.2. Record Keeping**

The Investigators will maintain appropriate medical and research records for this trial, in compliance with GCP and regulatory and institutional requirements for the protection of confidentiality of participants. The Chief Investigator, co-Investigators and clinical research nurses will have access to records. The Investigators will permit authorised representatives of the Sponsor(s), as well as ethical and regulatory agencies to

examine (and when required by applicable law, to copy) clinical records for the purposes of quality assurance reviews, audits and evaluation of the study safety and progress.

Following completion of the study, the trial master file, CRFs and all personal data such as contact details will be kept for a minimum of 5 years and until the youngest participant turns 21 years old, at Ardington Archives storage (Faringdon, Oxford) according to the relevant OVG/OVC SOP. Storage of this data will be reviewed every 5 years and files will be confidentially destroyed if storage is no longer required. Electronic data will be stored securely for the same period in University of Oxford electronic archives.

If participants consent to have their samples stored and used in future research, their consent form as well as the information stored within it, will be recorded, retained and stored securely as per Biobanking procedures and SOP.

### **11.3. Source Data and Case Report Forms (CRFs)**

All protocol-required information will be collected in CRFs designed by the Investigator. All source documents will be filed in the CRF. Source documents are original documents, data, and records from which the participant's CRF data are obtained. For this study, these will include, but are not limited to, participant consent form, blood results, GP response letters, laboratory records, diaries, medical records and correspondence. In the majority of cases, CRF entries will be considered source data as the CRF is the site of the original recording (i.e. there is no other written or electronic record of data). In this study this will include, but is not limited to medical history, medication records, vital signs, physical examination records, urine assessments, blood results, adverse event data and details of vaccinations. All source data and participant CRFs will be stored securely.

Source data verification requirements will be defined in the trial risk assessment and monitoring plan.

### **11.4. Data Protection**

The study protocol, documentation, data and all other information generated will be held in strict confidence. No information concerning the study or the data will be released to any unauthorised third party, without prior written approval of the sponsor.

### **11.5. Data Quality**

Data collection tools will undergo appropriate validation to ensure that data are collected accurately and completely. Datasets provided for analysis will be subject to quality control processes to ensure analysed data is a true reflection of the source data.

Trial data will be managed in compliance with local data management SOPs. If additional, study specific processes are required, an approved Data Management Plan will be implemented

### **11.6. Archiving**

Study data may be stored electronically on a secure server, and paper notes will be kept in a key-locked filing cabinet at the site. All essential documents will be retained for a minimum of 5 years after the study has finished. The need to store study data for longer in relation to licensing of the vaccine will be subject to ongoing review. For effective vaccines that may be licensed, we may store research data securely at the site at least 15 years after the end of the study, subject to adjustments in clinical trials regulations.

General archiving procedures will be conducted in compliance to SOP OVC020 Archiving.

## **12. QUALITY CONTROL AND QUALITY ASSURANCE PROCEDURES**

### **12.1. Investigator procedures**

Approved site-specific standard operating procedures (SOPs) will be used at all clinical and laboratory sites.

### **12.2. Monitoring**

Regular monitoring will be performed according to GCP by the monitor. Following written SOPs and an approved, risk-based monitoring plan, the monitor will verify that the clinical trial is conducted and data are generated, documented and reported in compliance with the protocol, GCP and the applicable regulatory requirements. The site will provide direct access to all trial related source data/documents and reports for the purpose of monitoring and auditing by the Sponsor and inspection by local and regulatory authorities.

### **12.3. Protocol deviation**

Any deviations from the protocol will be documented in a protocol deviation form and filed in the trial master file. Each deviation will be assessed as to its impact on participant safety and study conduct. Significant protocol deviations will be listed in the end of study report.

### **12.4. Audit & inspection**

The QA manager conducts systems based internal audits to check that trials are being conducted according to local procedures and in compliance with study protocols, departmental SOPs, GCP and applicable regulations.

The Sponsor, trial sites, and ethical committee(s) may carry out audit to ensure compliance with the protocol, GCP and appropriate regulations.

GCP inspections may also be undertaken by the MHRA to ensure compliance with protocol and the Medicines for Human Use (Clinical Trials) Regulations 2004, as amended. The Sponsor will assist in any inspections and will support the response to the MHRA as part of the inspection procedure.

